## Abstract

**Introduction:**

Propofol-based total intravenous anesthesia (TIVA) with remifentanil is widely used for general anesthesia but is frequently associated with hypotension and bradycardia. Remimazolam, an ultra–short-acting benzodiazepine, provides rapid onset and offset, with the additional advantage of reversal by flumazenil, and may result in less hemodynamic depression. Previous randomized studies have largely focused on the induction phase or the incidence of hypotension, with limited data on continuous intraoperative hemodynamic changes during laparoscopic gynecologic surgery. The study is designed to compare prospectively the intraoperative hemodynamic profiles of remimazolam-based versus propofol-based TIVA in patients undergoing robotic gynecologic surgery in the Trendelenburg position.

**Methods and Analysis:**

This prospective, single-center, randomized, single-blind, parallel-group superiority trial will be conducted at CHA Ilsan Medical Center, a secondary care university-affiliated hospital. In total, 58 adult patients (aged 19–65 years, American Society of Anesthesiologists physical status I–II) scheduled for elective robotic laparoscopic hysterectomy under general anesthesia will be enrolled and randomly assigned (1:1) to receive either remimazolam- or propofol-based total intravenous anesthesia, both in combination with remifentanil. Continuous invasive mean arterial pressure (MAP) will be monitored using a FloTrac™ sensor (Edwards Lifesciences, Irvine, CA, United States). The primary outcome will be the time-weighted average MAP (TWA-MAP), analyzed using analysis of covariance adjusted for baseline MAP. Secondary outcomes will include the area under the curve for hypertensive and hypotensive burden, as well as the incidence of adverse hemodynamic events, including hypotension, hypertension, bradycardia, and tachycardia. Generalized estimating equations (GEE) will be used to evaluate hemodynamic and respiratory parameters across predefined time points.

**Discussion:**

This trial is expected to provide prospective, randomized evidence to compare continuous intraoperative blood-pressure trajectories between remimazolam- and propofol-based TIVA during robotic gynecologic surgery. It is anticipated that the findings will clarify the relative hemodynamic stability of these anesthetic agents under the combined physiological challenges of Trendelenburg positioning and pneumoperitoneum. The findings may inform anesthetic drug selection and intraoperative blood pressure management strategies, enhancing cardiovascular stability and improving postoperative outcomes.

**Clinical Trial Registration:**

ClinicalTrials.gov, identifier NCT07251101.

## Introduction

1

Propofol-based total intravenous anesthesia (TIVA) combined with remifentanil is widely used for general anesthesia (Lan et al., 2024). However, propofol frequently induces hypotension and bradycardia (Peng et al., 2023; Lan et al., 2024). Remimazolam, a novel ultra–short-acting benzodiazepine, has a rapid onset and offset of action, and its sedative effect can be promptly reversed with flumazenil (Peng et al., 2023; Li et al., 2025). Recent studies indicate that remimazolam may be associated with a lower incidence of hypotension than propofol, offering improved hemodynamic stability (Liu et al., 2021; Choi et al., 2023; Peng et al., 2023; Fechner et al., 2024; Li et al., 2025).

Robotic gynecologic surgery presents distinct anesthetic challenges. To facilitate the procedure, patients are positioned in the Trendelenburg position, and pneumoperitoneum is established by insufflating carbon dioxide (CO_2_) into the peritoneal cavity; these conditions produce complex hemodynamic alterations. The Trendelenburg position increases stroke volume and central venous pressure, which may subsequently elevate cardiac output and mean arterial pressure (MAP) (Falabella et al., 2007; Haas et al., 2011). Conversely, CO_2_ insufflation increases intra-abdominal pressure, leading to elevated systemic vascular resistance, reduced stroke volume, and decreased cardiac output (Darlong et al., 2012). These physiological changes may compromise cardiovascular stability, emphasizing the importance of vigilant anesthetic management.

Therefore, this randomized controlled trial will be conducted to compare the hemodynamic effects of propofol- versus remimazolam-based TIVA in patients undergoing gynecologic laparoscopic surgery in the Trendelenburg position. Propofol was selected as the comparator because it is the current standard agent for TIVA at our institution and internationally. A direct comparison will enable assessment of whether remimazolam confers clinically meaningful advantages or poses specific risks relative to established practice. The null hypothesis is that there will be no difference in intraoperative MAP between the propofol and remimazolam groups.

## Methods

2

### Trial design, setting, and recruitment

2.1

This study is a prospective, single-center, randomized, single-blind, parallel-group superiority trial that will be conducted at CHA Ilsan Medical Center. In total, 58 patients undergoing robotic laparoscopic hysterectomy will be enrolled between October 2025 and October 2026. The Consolidated Standards of Reporting Trials (CONSORT) flowchart and study timeline are presented in Figure 1 and Supplementary Table S1. This protocol was developed in accordance with the Standard Protocol Items: Recommendations for Interventional Trials (SPIRIT) guidelines, and the trial will be reported according to the CONSORT 2025 statement.

**FIGURE 1 F1:**
[figure not shown]
CONSORT 2025 flow diagram.

Neither patients nor the public will be involved in the design, conduct, reporting, or dissemination of the research. A plain-language summary will be provided to participants following trial completion.

No external advertising will be used for recruitment. Eligible patients will be identified at the time of hospital admission. A trained investigator will provide detailed information about the study and will obtain written informed consent before surgery.

### Eligibility criteria

2.2

Eligible participants will be adult patients scheduled to undergo robotic laparoscopic hysterectomy under general anesthesia. Based on the inclusion criteria, patients aged 19–65 years, with a body mass index (BMI) of 18.5–35 kg/m^2^, and of American Society of Anesthesiologists Physical Status (ASA-PS) I or II will be included. The upper age limit of 65 years was selected because aging affects cardiovascular physiology and anesthetic pharmacodynamics, thereby reducing population heterogeneity (Doi et al., 2020). Similarly, the BMI range of 18.5–35 kg/m^2^ was chosen because extremes of body weight are associated with altered pharmacokinetic and pharmacodynamic characteristics that may influence hemodynamic responses to anesthetic agents (Park et al., 2018; Kim, 2021). Patients will be excluded if they present with preoperative systolic blood pressure (SBP) ≥ 160 mmHg or <90 mmHg, heart rate (HR) < 60 beats per minute or ≥100 beats per minute, hypoxemia defined as oxygen saturation (SpO_2_) < 90%, or a history of ischemic heart disease, cardiac conduction abnormalities, or severe respiratory disease, including uncontrolled asthma or chronic obstructive pulmonary disease. Additional exclusion criteria will include the administration of inhalational anesthetics during anesthesia and intraoperative conversion from robotic laparoscopic hysterectomy to open surgery.

This single-center trial will be conducted at CHA Ilsan Medical Center, a university-affiliated secondary hospital equipped with advanced robotic surgical platforms and electronic anesthesia documentation systems. All anesthesia will be administered by board-certified anesthesiologists with ≥3 years of clinical experience in total intravenous anesthesia using propofol and remimazolam infusion techniques. Participating surgeons will be experienced in robotic laparoscopic hysterectomy, each having performed >50 procedures before study initiation.

### Study process

2.3

After receiving a comprehensive explanation of the study objectives and procedures from an attending anesthesiologist, patients who voluntarily agree to participate and provide written informed consent will undergo eligibility screening. Participants who meet the inclusion criteria will be randomly allocated to either the remimazolam group or the propofol group. All intraoperative management will be conducted independently by anesthesiologists who are not involved in outcome assessment.

### Intraoperative monitoring and anesthetic management

2.4

Upon arrival in the operating room, all patients will undergo standard monitoring, including electrocardiography, pulse oximetry, invasive arterial blood pressure monitoring, and capnography. Preoxygenation with 100% oxygen will be performed for 3 min before induction.

For anesthesia induction, patients in the remimazolam group will receive remimazolam at 6 mg/kg/h (Lee and Kim, 2024) and remifentanil via target-controlled infusion (TCI) at an effect-site concentration (Ce) of 4 ng/mL. Patients in the propofol group will receive propofol via TCI at a Ce of 4 μg/mL together with remifentanil at 4 ng/mL. TCI will be performed using the Schneider pharmacokinetic model for propofol and the Minto pharmacokinetic model for remifentanil (Minto et al., 1997; Schnider et al., 1998). After loss of consciousness, rocuronium 0.6–0.8 mg/kg will be administered, and tracheal intubation will be performed when the train-of-four count reaches 0.

During maintenance, the remimazolam group will receive remimazolam at 1–2 mg/kg/h, whereas the propofol group will receive propofol via TCI at a Ce of 2.5–3.5 μg/mL. Anesthetic depth will be adjusted to maintain a Patient State Index (PSI) between 25 and 50 (SedLine, Masimo Corporation, Irvine, CA, United States). The Ce of remifentanil will be titrated in both groups according to intraoperative hemodynamic responses. Rocuronium will be continuously infused to maintain deep neuromuscular blockade (train-of-four count 0).

Mechanical ventilation will be set with a tidal volume of 8 mL/kg and an inspiratory-to-expiratory ratio of 1:2. The respiratory rate will be adjusted to maintain end-tidal carbon dioxide (ETCO_2_) at between 35 and 45 mmHg. A positive end-expiratory pressure of 5 cmH_2_O will be applied in all patients, and core body temperature will be maintained at between 36 °C and 37 °C.

At the end of surgery, ramosetron 0.3 mg will be administered for prophylaxis against postoperative nausea and vomiting (PONV). Neuromuscular blockade will be reversed with sugammadex 2–4 mg/kg, and flumazenil 0.3 mg will be administered in the remimazolam group to reverse residual sedative effects. Immediate postoperative analgesia will be initiated with intravenous fentanyl 50 μg, followed by standardized intravenous patient-controlled analgesia containing fentanyl, ramosetron, and nefopam.

To ensure protocol adherence, study medications will be prepared by an operating room anesthesia nurse according to a standardized protocol. Anesthesia providers will undergo pre-study training and will receive pocket reference cards outlining dosing procedures. The principal investigator will perform weekly adherence reviews, including verification of dosing accuracy and blinding, with all deviations recorded.

Standard perioperative management, including administration of intravenous fluids, vasopressors (e.g., ephedrine, phenylephrine), antibiotics, antihypertensive agents (e.g., nicardipine, labetalol), antiemetics (e.g., ramosetron), and analgesics, will be permitted according to institutional protocols. In the remimazolam group, normal saline will be used exclusively as the carrier fluid to avoid drug precipitation. The use of inhalational anesthetics, additional sedatives, including midazolam and dexmedetomidine, or investigational agents will be prohibited throughout the trial.

### Harms and criteria for discontinuation or modification

2.5

Remimazolam and propofol are routinely used intravenous anesthetics for robotic laparoscopic surgery at our institution. Therefore, participation in our trial is not anticipated to introduce additional risk. However, hypotension and bradycardia may occur following administration of sedatives or opioids, and hypertension or tachycardia may arise in response to surgical stimuli. Hypotension (SBP <90 mmHg or MAP <65 mmHg) will be managed by reducing the remifentanil infusion rate. Severe hypotension (SBP <80 mmHg or MAP <60 mmHg) will be treated with intravenous ephedrine 5–10 mg or phenylephrine 30–100 μg. Hypertension (SBP >140 mmHg or MAP >100 mmHg) will be managed by increasing the remifentanil infusion rate, whereas severe hypertension (SBP >160 mmHg or MAP >105 mmHg) will be treated with intravenous nicardipine 300–500 μg or labetalol 5–10 mg. Bradycardia (HR < 45 beats/min) will be treated with intravenous glycopyrrolate 0.2 mg or atropine 0.25 mg, and tachycardia (HR > 100 beats/min) will be managed using intravenous esmolol 10–20 mg.

Study interventions may be modified or discontinued in cases of severe hypotension (SBP <80 mmHg or MAP <60 mmHg) unresponsive to protocol-directed vasopressor therapy, severe bradycardia (HR < 40 beats/min) unresponsive to atropine or glycopyrrolate, severe hypoxemia (SpO_2_ < 90% for more than 1 min), a severe allergic reaction to study medications, or if the attending anesthesiologist determines that continuation of the assigned intervention is unsafe. In such situations, anesthesia may be transitioned to an alternative regimen at the clinician’s discretion, and the event will be documented in the case report form (CRF).

### Outcomes

2.6

The primary outcome of the study will be the time-weighted average (TWA)-MAP measured throughout anesthesia using an arterial line connected to a FloTrac™ sensor (Edwards Lifesciences, Irvine, CA, United States). For each participant, TWA-MAP will be calculated as the integral of MAP over elapsed time divided by the total observation duration, using the trapezoidal method. Data will be collected at approximately 1-min intervals when available, and measurements identified as technical artifacts (e.g., arterial line flushing, signal disconnection, damping artifacts, or recording errors) based on inspection of the arterial pressure waveform and corresponding clinical records will be excluded following data quality assessment. The primary analysis will compare TWA-MAP between the remimazolam and propofol groups to test the hypothesis that remimazolam-based TIVA will maintain a ≥20% higher intraoperative MAP than propofol-based TIVA.

Secondary outcomes will include the cumulative intraoperative burden of hypertension and hypotension. Hypertensive burden will be quantified as the area under the curve above the hypertension threshold (SBP ≥140 mmHg or MAP ≥100 mmHg), expressed in mmHg·min using the trapezoidal method. Hypotensive burden will be quantified as the area under the curve below the hypotension threshold (SBP <90 mmHg or MAP <65 mmHg), also expressed in mmHg·min. Group comparisons will assess whether remimazolam-based TIVA differs from propofol-based TIVA in hypertensive and hypotensive burdens. The time frame for secondary outcomes will extend from the start of induction to exit from the operating room.

In addition, intraoperative adverse hemodynamic events, including hypotension, hypertension, bradycardia, and tachycardia, will be recorded. Preoperative data will include patient characteristics, such as height, weight, age, diagnosis, scheduled surgical procedure, medical history, preoperative medication use, and baseline vital signs. Intraoperative data will include the surgical procedure performed, anesthesia duration, operative duration, degree of head-down tilt, vasopressin administration for bleeding control, estimated blood loss, fluid administration, and remifentanil dosage. Postoperative data will include post-anesthesia care unit (PACU) stay duration, PACU vital signs, and administration of additional medications, such as antiemetics and analgesics.

As a sensitivity analysis, hemodynamic and respiratory parameters will be assessed at prespecified time points to evaluate temporal changes and validate consistency with the primary outcome. Measurements will be obtained before induction (T0); every minute for 10 min from induction drug initiation (T1–T10); every 10 min for 30 min after establishment of both the Trendelenburg position and pneumoperitoneum (T20–T23); at pneumoperitoneum release (T30) and 10 min afterward (T31); and upon PACU arrival (T40), followed by every 10 min for 30 min (T41–T43). Arterial blood gas analysis will be performed at T10, T21, and T31. During anesthesia induction and maintenance, HR, SBP, diastolic blood pressure (DBP), MAP, respiratory rate (RR), SpO_2_, ETCO_2_, cardiac output (CO), cardiac index (CI), and stroke volume variation (SVV) will be recorded. In the PACU, HR, SBP, DBP, MAP, RR, and SpO_2_ will be recorded at the same prespecified intervals.

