### Sample size

2.7

A previous study reported the median and interquartile range of intraoperative MAP during total intravenous anesthesia in patients receiving remimazolam or propofol (remimazolam: 81.3 [76.9–92.5] mmHg; propofol: 76.8 [67.8–82.5] mmHg) (Tsukimoto et al., 2024). Based on these findings, we will estimate the means and standard deviations using the method described by Wan et al. (2014). The required sample size was calculated using G*Power software (version 3.1; Heinrich Heine University, Düsseldorf, Germany). With 80% power and a two-sided significance level of 0.05, 26 participants per group are required (effect size = 0.7). To account for a 10% dropout rate, we will recruit a total of 58 patients.

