### Statistical analysis

2.11

The primary outcome, TWA-MAP, will be analyzed using analysis of covariance, with group assignment as the fixed factor and baseline MAP, age, BMI, ASA-PS, and histories of hypertension and diabetes as covariates. Secondary outcomes, including hypertensive and hypotensive burden (area under the curve above or below predefined thresholds), will be compared between groups using Student’s t-test for normally distributed variables or the Mann–Whitney U test for non-normally distributed variables. Categorical outcomes, such as intraoperative hypotension, hypertension, bradycardia, tachycardia, PONV, and postoperative analgesic use, will be evaluated using the chi-square test or Fisher’s exact test, as appropriate.

Repeated-measures variables across prespecified time points (T0–T43), including HR, SBP, DBP, MAP, CO, CI, SVV, ETCO_2_, and arterial blood gas parameters, will be analyzed using generalized estimating equations (GEE) to assess group, time, and group-by-time interaction effects. An appropriate working correlation structure will be selected to account for within-subject correlations over time. As a sensitivity analysis, GEE analysis of serial blood pressure data will be performed to evaluate consistency with findings from the primary TWA-MAP analysis.

The primary efficacy analysis will follow the per-protocol (PP) principle, including all randomized participants who fully adhere to the study protocol. Participants with major protocol deviations, such as conversion to open surgery, administration of inhalational anesthetics, incomplete intraoperative hemodynamic monitoring, or early withdrawal, will be excluded from the PP analysis. Participants who discontinue the intervention due to serious adverse events will also be excluded. No intention-to-treat analysis is planned. The safety population will include all participants who receive at least one dose of the assigned anesthetic agent and will be analyzed according to the treatment actually administered.

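### Section 2.6 says the primary analysis tests a ≥20% higher MAP, but the stated null is zero difference, no margin test is planned, and the sample size rests on a difference of about 10%

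*Protocol article*

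**What the plan says.** The protocol article describes its primary comparison in five places.

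- **Section 2.6, Outcomes:** the purpose of the primary analysis of TWA-MAP is "to test the hypothesis that remimazolam-based TIVA will maintain a ≥20% higher intraoperative MAP than propofol-based TIVA".
- **Section 1, Introduction:** "The null hypothesis is that there will be no difference in intraoperative MAP between the propofol and remimazolam groups".
- **Section 2.1, Trial design:** a "prospective, single-center, randomized, single-blind, parallel-group superiority trial", with no superiority margin.
- **Section 2.7, Sample size:** the planning data are medians with interquartile ranges from an earlier study, "remimazolam: 81.3 [76.9–92.5] mmHg; propofol: 76.8 [67.8–82.5] mmHg". They are to be converted to means and standard deviations. The calculation uses an effect size of 0.7, a two-sided 5% level and 80% power, and gives 26 per group. The figure of 20% does not appear.
- **Section 2.11, Statistical analysis:** "The primary outcome, TWA-MAP, will be analyzed using analysis of covariance, with group assignment as the fixed factor", plus baseline covariates. No 20% margin, ratio contrast or confidence-limit rule is given.

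**The concern.** A hypothesis that MAP is at least 20% higher under remimazolam has a direction and a margin. Testing it means rejecting a null in which the remimazolam mean is no more than 1.20 times the propofol mean. The null in the Introduction has neither direction nor margin, and rejecting it says only that the means differ.

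The success criterion of the primary outcome is therefore not fixed. A significant difference of 8 mmHg would reject the Introduction's null but fall well short of the hypothesis in 2.6. In the other direction, a small p-value against zero could be reported as confirming an advantage of 20% or more that was never tested. Which reading applies has to be settled before the data are seen.

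**Working it through.** **Inputs.** From section 2.7: quartiles and medians of 76.9, 81.3, 92.5 mmHg (remimazolam) and 67.8, 76.8, 82.5 mmHg (propofol); effect size 0.7; 26 per group. From section 2.6: the 20%. The article does not print the conversion formula or the earlier study's sample size, so I assume the large-sample form: mean = (q1 + median + q3)/3 and SD = (q3 − q1)/1.35.

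**1. Reproduce the planning effect.**
- Remimazolam: mean = (76.9 + 81.3 + 92.5)/3 = 83.57; SD = 15.6/1.35 = 11.56.
- Propofol: mean = (67.8 + 76.8 + 82.5)/3 = 75.70; SD = 14.7/1.35 = 10.89.
- Pooled SD = √[(11.56² + 10.89²)/2] = 11.23.
- Difference = 7.87 mmHg; effect size = 7.87/11.23 = 0.70.

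This matches the stated 0.7, so these are very probably the planning values.

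**2. Express it as a percentage.** 7.87/75.70 = 10.4%. On the medians it is 4.5/76.8 = 5.9%.

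**3. Size of a 20% difference.** 0.20 × 75.70 = 15.14 mmHg, or 15.14/11.23 = 1.35 SD. Against a zero null, an effect of that size would need only about 10 per group, so the trial was not sized on it.

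**4. What is significant against zero at 26 per group.** SE = 11.23 × √(2/26) = 3.11 mmHg. With t(0.975, 50 df) = 2.009, the smallest significant difference is about 6.25 mmHg, or 8.3% of 75.70.

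**5. What would support 20%, if the true difference is 7.87 mmHg.**
- Chance that the estimate reaches 15.14: z = (15.14 − 7.87)/3.11 = 2.34, so about 1%.
- For the lower 95% limit to exceed 15.14, the observed difference must be about 15.14 + 6.25 = 21.39 mmHg (28%). The chance of that is about 0.001%.

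**6. Power of a genuine 20% margin test.** Null: remimazolam mean ≤ 1.20 × propofol mean; one-sided 0.025; 26 per group; SD 11.23.

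| True difference | Power |
|---|---|
| 10.4% (planning) | below 0.01% |
| 20% | 2.5% |
| 25% | 19% |
| 30% | 58% |
| 35% | 90% |

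**7. Sensitivity.**
- If the earlier study had 15 to 100 patients per arm, the small-sample SD formula gives an effect size of 0.63 to 0.69. The 10.4% does not change, because it does not depend on the SD.
- If adjustment for baseline reduces the residual variance (assumed correlation 0.3 to 0.7), the smallest significant difference falls to 7.9% to 5.9%. Power against the 20% margin at the planning difference stays below 0.01%.

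**The case against.** The strongest reply is that the Introduction and sections 2.1, 2.7 and 2.11 all read as one ordinary two-sided comparison. The 20% clause is then a single outlier, perhaps an expected effect loosely attached to the word hypothesis. The data, the estimator and the p-value are the same either way. This is a fair account of how the sentence may have arisen, and it is why the repair is small. It does not remove the conflict: the sentence says what the primary analysis is for, nothing calls 20% an expectation or a relevance threshold, and as an expectation it still disagrees with the roughly 10% behind section 2.7.

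Three qualifications stand:
- Section 2.11 does not state the null value of the group term. That it tests zero is the default reading, taken together with the Introduction. An ANCOVA estimate and its confidence interval could be compared with a margin, but no such comparison is described.
- Support for 20% is not impossible. An observed difference of about 28% would put the lower confidence limit above a fixed 15.14 mmHg.
- The means and SDs are reconstructed, not printed in the article, and the probabilities in step 5 hold only if the planning difference is true.

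Leaving the matter to a fuller analysis plan does not help. These are conflicting statements, not an omission, and one plan could not satisfy both.

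**Conclusion.** The concern holds and must be fixed. As planned, the primary test does not test the hypothesis that section 2.6 assigns to it, and the trial was sized on a difference about half as large (10.4% against 20%). A result anywhere from about 8% upwards would count as positive against zero, while a demonstration of at least 20% would need an observed difference of about 28%. At the planning effect that is practically unattainable. These figures assume the large-sample conversion, 26 analysed per group and no variance reduction from covariates; relaxing the first and last of these does not alter the conclusion. The conflict between section 2.6 and the Introduction needs no calculation at all.

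**What to change.** Replace the sentence in section 2.6 with wording such as: *The primary analysis tests the two-sided null hypothesis of no difference in mean TWA-MAP between groups; the adjusted difference in mmHg will be reported with its 95% confidence interval.* Delete the 20%, or keep it only as a benchmark against which the interval is described. This brings 2.6 into line with the Introduction and sections 2.1, 2.7 and 2.11.

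The cost is one sentence, with no change to data collection. The full protocol, analysis plan and registration should be aligned if they repeat the 20%; they were not available to check.

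The alternative is to define a real 20% margin test, with its null, contrast and decision rule, and to re-size the trial. On the reconstructed planning values, where the expected difference lies below the margin, no sample size would give adequate power, so the planning assumption would have to change too.

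Restating the hypothesis does not make the present sample size adequate. As a separate matter, an effect size of 0.7 with a two-sided 5% level and 80% power needs 34 per group. The stated 26 matches a one-sided test and gives about 70% power two-sided.

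### Some eligible patients already meet the hypertension definition when the outcome window opens, which dilutes the comparison of hypertension incidence

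*Protocol article*

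**What the plan says.** - **Entry (2.2).** The blood-pressure exclusion is "preoperative systolic blood pressure (SBP) ≥ 160 mmHg or <90 mmHg". SBP 140–159 is therefore eligible. MAP has no entry limit.
- **Limit and scale (2.6).** "Hypertensive burden will be quantified as the area under the curve above the hypertension threshold (SBP ≥140 mmHg or MAP ≥100 mmHg"), with the area "expressed in mmHg·min using the trapezoidal method".
- **Window (2.6).** "The time frame for secondary outcomes will extend from the start of induction to exit from the operating room".
- **Events (2.6).** Separately, "intraoperative adverse hemodynamic events, including hypotension, hypertension, bradycardia, and tachycardia, will be recorded". The abstract lists the incidence of these events among the secondary outcomes.
- **Analysis (2.11).** Burden is compared by "Student’s t-test for normally distributed variables or the Mann–Whitney U test for non-normally distributed variables". Incidence "will be evaluated using the chi-square test or Fisher’s exact test, as appropriate". Neither uses a baseline value. Only the primary analysis of covariance does, with "baseline MAP, age, BMI, ASA-PS, and histories of hypertension and diabetes as covariates".
- **Harms (2.5).** The hypertension limit is written there as strictly above 140 or 100 mmHg, whereas 2.6 uses at or above.

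**The concern.** At the first minute of the window the reading is still essentially the awake pressure. An eligible patient at 150/85 is then above the limit whichever drug follows. The article states no rule for such readings; the only exclusion in 2.6 is for technical artifacts. The overlap exists whether the cut-off is read as at or above 140 or as strictly above 140.

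Patients who count as hypertensive before the drug acts raise the incidence equally, in expectation, in both arms and carry no information about the drugs. That pulls the observed difference towards zero. It matters because the Discussion cites a retrospective study in this surgical position that linked remimazolam to more intraoperative hypertension. An attenuated comparison could miss the harm that the trial is well placed to examine.

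**Working it through.** **Inputs from the protocol.** Entry range SBP 90–159, hypertension limit SBP 140 or MAP 100, window from the start of induction, and 26 analysed per arm (Sample size). The protocol gives no baseline pressure distribution and no expected hypertension rate, so it has no figure of its own to reproduce. Everything below that needs one is an assumption.

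**Step 1: share above the limit at entry, SBP only.** Assume normal SBP with SD 15, truncated at 90 and 160. With F the normal distribution function, share f = [F(160) − F(140)] / [F(160) − F(90)].

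| Mean SBP | Calculation | f |
|---|---|---|
| 120 | (0.9962 − 0.9088) / (0.9962 − 0.0228) | 9.0% |
| 125 | (0.9902 − 0.8413) / (0.9902 − 0.0098) | 15.2% |
| 130 | (0.9772 − 0.7475) / (0.9772 − 0.0038) | 23.6% |
| 135 | (0.9522 − 0.6306) / (0.9522 − 0.0013) | 33.8% |

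Widening the assumptions to means of 120–140 and SDs of 12–18 gives 5–48%. The MAP route can only add to these shares.

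**Step 2: incidence.** If a share f of each arm counts from the start and the rest have on-drug incidence p, independently of f, the observed incidence is f + (1 − f)p. The risk difference is then (1 − f)(p₂ − p₁). Assume p₁ = 20%, p₂ = 55% and n = 26 per arm. Approximate two-sided power at 5% is Φ{[Δ − 1.96√(2p̄(1 − p̄)/n)] / √([p₁(1 − p₁) + p₂(1 − p₂)]/n)}, using the observed incidences.

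| f | Observed incidences | Difference | Power |
|---|---|---|---|
| 0 | 20.0% vs 55.0% | 35.0 points | 76% |
| 9.0% | 27.2% vs 59.1% | 31.9 | 65% |
| 15.2% | 32.2% vs 61.8% | 29.7 | 58% |
| 23.6% | 38.9% vs 65.6% | 26.7 | 49% |
| 33.8% | 47.0% vs 70.2% | 23.2 | 39% |

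Simulation of the chi-square test agrees: about 77% falling to 40–63% over the same shares. The starting level depends on the assumed rates. With 30% versus 60%, power is 59% at f = 0 and 34% at f = 30%.

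**Step 3: burden.** If SBP starts at S and falls linearly to 140 in t minutes, the added area is (S − 140) × t / 2. From 145 in 1 minute this is 2.5 mmHg·min; from 159 in 5 minutes it is 47.5 mmHg·min. If the early fall is similar in both arms, the same expected area is added to each and the mean difference does not change. In a simulation, 30% versus 60% of patients had a lognormal burden (log-means 4 and 4.5, log-SD 1), the rest had zero, and up to 20 or 50 mmHg·min was added in 0–40% of patients. The t-test stayed near 50–54% power. Mann–Whitney power fell from about 69% to 57–61% at shares of 30–40%, mainly because zeros become small positive values.

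**Step 4: chance imbalance.** Randomisation equalises the starting share only in expectation. With a 20% share and 26 per arm, the between-arm difference has standard deviation √(2 × 0.2 × 0.8 / 26) = 0.11, or 11 points. The allocation is unstratified and the planned tests do not correct for this.

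**Step 5: what recovers the loss.** In the 20% versus 55% scenario, stratifying incidence by T0 status gives 58–71% power, which is about half or more of the loss. A new-onset count gives 65–74%, even when 30% of remimazolam and 5% of propofol patients who start above the limit never fall below it and are scored as non-events.

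**The case against.** - **The size is assumed.** This stands. With no baseline distribution in the article, a reader might infer that many patients are affected, and the documents do not support that word. What they support is that such patients are eligible and are expected to some degree, since history of hypertension is a covariate.
- **Burden is an area, not a label.** This also stands. A reader might infer that the burden difference is diluted in the same way as incidence; Step 3 shows that the mean difference is not. Part of the early area may even be a genuine drug effect. For illustration, from SBP 150, falls of 1.2 and 4 mmHg per minute give 10 × 8.33 / 2 = 41.7 and 10 × 2.5 / 2 = 12.5 mmHg·min above 140. Deleting early readings would erase that difference.
- **The event-counting rule may sit in a fuller document.** This is fair as far as it goes. The article does not say how many readings make an event. But the limit, the window and the unadjusted tests are stated, and together they produce the overlap unless something else overrides them.
- **Starting at induction is deliberate.** The Discussion says the trial covers induction, maintenance and emergence, and the T0–T43 generalized estimating equations will show baseline and later divergence. That is a reason to keep the window. It does not repair the incidence comparison.
- **Counting only after a fall below the limit could itself bias.** This stands. That fall occurs after randomisation and may depend on the drug. A patient hypertensive throughout would score zero. Such a rule should not replace the main definition.

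**Conclusion.** The point holds for hypertension incidence. The entry range and the outcome limit overlap, the window opens before any drug effect, and the planned test ignores baseline. The risk difference shrinks by about the share already above the limit, which is 9–34% by SBP alone under the stated assumptions. In the 20% versus 55% scenario, power falls from about 77% to 40–63%. The size is conditional on figures that the protocol does not give; the overlap is not.

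For burden, the consequence is noise and some loss of rank-test power, provided the early fall is similar in both arms. A reader might infer bias towards one drug. The documents do not support that: the starting share is equal in expectation, so the effect is attenuation plus unadjusted chance imbalance. The primary outcome, TWA-MAP, is not affected, since it uses no hypertension limit and is adjusted for baseline MAP.

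**What to change.** In 2.6 and 2.11:

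1. Keep the plan's outcome definitions and window.
2. Compare hypertension incidence stratified by status at T0 (above or below the limit), for example by Cochran–Mantel–Haenszel, and show the risks within each stratum.
3. Compare hypertensive burden adjusted for T0 pressure; a rank-based analysis of covariance would suit a skewed area.
4. Report the number of patients above the limit at T0 by arm.
5. Prespecify a supportive analysis of new-onset hypertension: a reading at or above the limit after at least one post-induction reading below both limits. Count patients who never fall below as hypertensive, or show them separately by arm. Do not score them as zero.
6. Reconcile the strict inequalities in 2.5 with the inclusive ones in 2.6.

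The cost is a few sentences and a little more analysis on data already being recorded, including T0. The new-onset analysis depends on a post-randomisation reading, so it should stay supportive.
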